#### 2.5.2 Healthy participants

Healthy participants will receive no treatment, but only the general information registration, a corresponding health physical examination, and collection of fecal and serum.

### 2.6 Outcome measurements

#### 2.6.1 Primary outcome

COPD Assessment Test (CAT) The change in the CAT scores before (week 0) and after (week 12) the intervention is chosen as the primary outcome.

The scale evaluates and reflects the severity of COPD patients’ conditions through 8 items, including 3 indicators of clinical symptoms: cough, sputum, and chest tightness, 2 indicators of tolerance: exercise tolerance, daily activities (status of limited activities at home), and 3 indicators of life quality: sleep quality, energy, and mood (confidence in outings). The response values of each item are ranging from 0 to 5 (0 = no impairment). Response values for all 8 items will be summed up to obtain the total scores of (ranging from 0 to 40). Higher scores indicate a greater impact of the disease on the patient’s health and life (46): 0–9 is considered a low impact, 10–20 is considered a moderate impact, 21–30 is considered a high impact, and 31–40 is considered a very high impact (47). In addition, week 4, week 8 and the follow-up period (week 38, week 64) will also collect data on this scale’s scores (Table 1).

#### 2.6.2 Secondary outcomes

##### 2.6.2.1 Indicators reflecting clinical symptoms

(1) Modified Medical Research Council (mMRC): The mMRC scale will be applied to assess the dyspnea status of COPD patients. The scale is categorized into five grades (0 to 4) according to the level of activity taken when the dyspnea happens, with grade 0 (the least severe) indicating that the patient experienced dyspnea only during strenuous exercise, and grade 4 (the most severe) indicating that the patient experienced dyspnea with just the slightest activity (48).

(2) St. George’s Respiratory Questionnaire (SGRQ): The SGRQ will be applied to assess the life quality of COPD patients. The scale consists of two parts, reflecting the impact of COPD on patients from three dimensions: the first part contains symptomatic questions, answered in the form of single-choice questions, which ask patients about the frequency and severity of the occurrence of cough, sputum, shortness of breath, and dyspnea; the second part is based on right and wrong questions, which include questions about activities (activity limitation due to dyspnea) and the impact of the disease (impaired socialization and psychological disorders due to airway disease). The 3 main dimensions is scored according to the weighting of the different questions, with the scores calculated using a weighted average method, resulting in a symptom score, an activity score, and an impact score, which are finally summarized to give a total score. Higher patient scores indicate poorer quality of life (49).

(3) 6-min walk test (6MWT): The 6MWT will be applied to assess the exercise tolerance of COPD patients. The test is commonly used to objectively assess patients with moderate-to-severe pulmonary disease. In the test, patients will be asked to walk as far as they can for 6 min along a 30-meter-long corridor. The 6-min walk distance (6MWD) (50), heart rate, respiratory rate, and the values of oxygen saturation (SpO_2_) will be recorded before and after the test (51). The degree of dyspnea will be assessed before and after the test by the Borg scale. The Borg scale consists of a magnitude of 0–10, with 0 being “no dyspnea at all” and 10 being the “the worst dyspnea.” In conjunction with 6MWD recordings, changes in dyspnea levels at rest and after sub-extreme exercise can be assessed, as well as the patient’s exercise tolerance under daily physical activity.

(4) Number of moderate or severe acute exacerbations of during the follow-up period: The number of moderate or severe acute exacerbations in the follow-up period will be counted, as one of the indicators for assessing the long-term effects of acupuncture-assisted treatment for COPD.

The moderate (patient needs to be treated with short acting bronchodilators plus antibiotics and/or oral corticosteroids) and severe (patient requires hospitalization or visits the emergency room) acute exacerbations of COPD are defined and classified referring to the *Global Strategy for the Diagnosis, Management, and Prevention of Chronic Obstructive Lung Disease: the GOLD science committee report 2022* (41).

The measurement nodes for the outcome indicators above are detailed in Table 1.

##### 2.6.2.2 Other indicators sent for testing

Fecal samples and fasting blood samples will be collected at baseline (week 0) and at the end of the intervention (week 12) for COPD patients, and only at baseline for healthy subjects.

(1) Changes in gut microbiota: The third generation of full-length 16S rRNA sequencing technology will be utilized to analyze the gut microbiota of participants.

Participants will be advised to maintain a normal diet (no specific changes from previous habits) and to avoid spicy, greasy or probiotic-containing foods such as yogurt prior to the collection of fecal samples. The sample should be collected approximately 4 g from the middle internal part of the feces using a disposable fecal kit and stored in a −80°C refrigerator within 30 min. The DNA of gut microbiota from fecal samples will be extracted by using dedicated kits, then a SMRT (single-molecule real-time) bell library will be constructed. SMRT sequencing will be performed on the PacBio Sequel II sequencing platform (Pacific Biosciences, USA). After raw data processing, clustering or noise reduction analyses will be performed to obtain ASVs (Amplicon Sequence Variants). Based on these sequences, species annotation, further cluster analysis and difference analysis can be performed. Indicators for the analysis of gut microbiota include structural diversity of the microbiota, and expression abundance of key strains as well as their intergroup differences.

(2) Changes in content of metabolomics: The untargeted metabolomics study will be performed on blood samples from participants by using liquid chromatography-tandem mass spectrometry (LC-MS/MS) technology (52, 53).

Disposable anticoagulation tubes will be utilized to collect the peripheral venous blood samples. A portion of the blood samples will be separated by centrifugation with serum dispensed into dry tubes. Multiple tubes of each sample will be prepared for backup and stored in a refrigerator at −80°C. The serum samples will be processed accordingly to extract the metabolites and then sent to the instrument for analysis. The raw files (.raw) obtained by mass spectrometry will be imported into Compound Discoverer 3.3 software for spectrum processing and database searching to get qualitative and quantitative results of metabolites. By multivariate statistical analysis, the differences in metabolic patterns among different groups will be revealed and the screening of differential metabolites will be performed. Hierarchical clustering and metabolite correlation analyses will be used to reveal the relationships between samples and between metabolites. Finally, systematic pathway annotation of all identified metabolites and differential analysis and KEGG (Kyoto Encyclopedia of Genes and Genomes) analysis of all differential metabolites will be performed to explain the biological significance of metabolite correlations.

(3) Changes in percentage of Th17/Treg immune cells: Flow cytometry will be utilized to quantify Th17 and Treg cells from the blood samples and the ratio of the two will be calculated.

A portion of the whole blood samples will be taken to make a single cell suspension. Blood cells will be stabilized using anticoagulants and then stained for cell surface markers using flow cytometry. The labeled cells will be detected and analyzed using a fluorescein analyzer. By setting up different fluorescence channels, the proportions of Th17 and Treg cells will be detected and calculated, respectively.

(4) Changes in expression levels of inflammatory cytokines: The enzyme-linked immunosorbent assay (ELISA) will be utilized to measure the levels of the following indicators in serum samples from the participants: TNF-α, IL-17A, IL-1β, IL-2, IL-10, IL-4, IL-6, interferon-γ (IFN-γ), α7 acetylcholine (ACHα7).

Corresponding ELISA kits will be prepared. Standards and quality control solution will be prepared according to the manufacturer’s instructions. Then The samples and standards will be added separately to the ELISA plates with antibodies for the detection of specific inflammatory factors. After the steps of washing plates, adding substrate and terminating the reaction, the absorbance values will be measured based on color intensity. Finally, a standard curve will be fitted and the concentration of the inflammatory factor in the sample will be calculated in terms of the standard curve.

### 2.7 Safety assessment

Safety will be assessed by vital signs examination and routine blood tests before and after the treatment period. Adverse events (AEs) associated with the intervention, including bleeding, hematoma, needle breakage, local infection, persistent pain, syncope, etc., must be reported promptly and recorded in the CRFs, which included symptoms, signs, time of occurrence, extent, duration, disposal measures, process and results of AEs (Note: acute exacerbation of COPD is not counted as an adverse event). Serious cases should to be reported to the Project Management Office and Ethics Committee of Chengdu University of Traditional Chinese Medicine within 24 h and their participation in trial will be aborted. Upon occurrence of an adverse event, participants will immediately receive appropriate treatment and decide whether to withdraw from the trial at their own discretion. Participants who abort the trial will continue to be investigated and followed up, and the results will be recorded accordingly.

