## 2 Materials and methods

### 2.1 Objectives

This trial aims to:

(1)Evaluate the immediate and long-term efficacy and safety of acupuncture in treating COPD;(2)Investigate whether acupuncture can improve the clinical symptoms of COPD patients by influencing the gut microbiota and metabolome, regulating the dynamic balance of immune cells Th17/Treg and the levels of related inflammatory cytokines.

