### 2.2 Trial design and setting

This is a prospective, parallel-controlled, multicenter, randomized controlled trial with blinded participants, outcome assessors, and statistician. A total of 72 COPD patients eligible will be randomly assigned to the manual acupuncture (MA) group and sham acupuncture (SA) group in a 1:1 ratio. The entire study period consists of 1 week of screening, 12 weeks of treatment and 52 weeks of follow-up. Both groups of patients will be assessed on the relevant scales throughout the study cycle (including at the time of enrollment, during the intervention period and the follow-up period), and changes in the clinical symptoms of COPD patients will be observed to clarify the effect of acupuncture on COPD. Furthermore, 36 healthy volunteers will also be recruited as a normal control group and will not receive any treatment. The trial will be conducted in four sub-centers: the Affiliated Hospital of Chengdu University of Traditional Chinese Medicine, the Sichuan Provincial People’s Hospital, the Chengdu Second People’s Hospital, and the Meishan Hospital of Traditional Chinese Medicine.

The study protocol is developed following The Consolidated Standards of Reporting Trials (CONSORT) Framework (38) and The Standards for Reporting Interventions in Clinical Trials of Acupuncture (STRICTA) (39), and will be reported in accordance with the Standard Protocol Items: Recommendations for Interventional Trials (SPIRIT) guidelines and checklist (40). The flow chart of trial procedures is shown in Figure 1, and the study schedule is depicted in Table 1.

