**Assessments**								
CAT		×	×	×	×	×	×	
mMRC		×	×	×	×	×	×	
SGRQ		×	×	×	×	×	×	
6-MWT		×			×	×	×	
Times of AECOPD						×	×	
Blinding assessment					×			
Safety assessment			×	×	×			
Adherence evaluation		×	×	×	×	×	×	

COPD, chronic obstructive pulmonary disease; CAT, COPD Assessment Test; mMRC, modified Medical Research Council; SGRQ, St. George’s Respiratory Questionnaire; 6MWT, 6-min walk test; AECOPD, acute exacerbation of chronic obstructive pulmonary disease.

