#### 2.4.3 Blinding

Patients, outcome assessors, data entry clerks and statistical analysts will be blinded. Letters A and B will be used instead of specific group names, and the same manipulation device will be applied to mask the difference in acupuncture between the two treatment groups of patients. During treatment, patients will be arranged to be in different rooms to avoid communication. The investigators, therapists, efficacy assessors and data statisticians will be separated throughout the whole study process. At the end of the 12-week treatment, patients will be asked if they received traditional acupuncture (yes, no, or unclear) to determine if the blinding was successful.

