Some inevitable limitations exist in this study. Firstly, only patients with moderate or severe COPD will be included in this study, and the applicability of the findings to mild and very severe patients will be questionable. Secondly, many other lung diseases will be excluded, and the participants may be somewhat different from the real COPD patient population. Finally, due to the nature of the acupuncture operation, it is not possible to blind the acupuncturist. To minimize any resulting bias, this study will strictly enforce allocation concealment, and blinding of patients, assessors, and statistical analysts. Registration and measurement of outcomes will be completed by personnel unaware of the subgroups and interventions.

In conclusion, the results of this trial will hopefully provide valid clinical evidence for supporting the efficacy of acupuncture-assisted treatment for stable COPD, and on this basis, explore the relationship between the acupuncture effect and gut microbiota, metabolome, and inflammation, which will provide a scientific basis for elucidating the mechanism of action of acupuncture therapy.

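### Adverse events are defined by association with the intervention and safety is scheduled only to week 12, so unrelated events, treatment-period exacerbations and late events fall outside the safety comparison

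*Protocol article*

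**What the plan says.** The first objective in Section 2.1 is to "Evaluate the immediate and long-term efficacy and safety of acupuncture in treating COPD". Section 2.2 gives the time frame: "The entire study period consists of 1 week of screening, 12 weeks of treatment and 52 weeks of follow-up".

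Section 2.7 sets out how safety is collected, in three parts:

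- Measurements: "Safety will be assessed by vital signs examination and routine blood tests before and after the treatment period".
- Events: "Adverse events (AEs) associated with the intervention, including bleeding, hematoma, needle breakage, local infection, persistent pain, syncope, etc., must be reported promptly". These are entered in the case report form with their course and outcome.
- An exclusion, given as a note: "acute exacerbation of COPD is not counted as an adverse event".

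In Table 1 the row "Safety assessment" has three marks. Read against the column order they fall at weeks 4, 8 and 12. The follow-up visits at weeks 38 and 64 carry no safety mark, although CAT, mMRC, SGRQ, the walk test and exacerbation counts are all collected there.

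Exacerbations are handled elsewhere. Section 2.6.2.1, item 4, counts moderate and severe ones in the follow-up period, and Table 1 marks that count at weeks 38 and 64. Section 2.5.1.3 covers those that lead to discontinuation, for which the time and the reason are noted.

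**The concern.** A between-arm safety comparison is cleanest when every untoward event is written down first and its cause is judged afterwards. Here the recording sentence is already limited by cause. Someone has to decide that an event is associated with the intervention before the rule applies to it. An event put down to the underlying disease, to another illness or to chance is not covered. An analysis plan cannot restore data that were never collected.

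The judgement could also differ by arm. Section 3 concedes that "it is not possible to blind the acupuncturist", and Section 2.8 makes the acupuncturist the first to act on needling events. If that person's view of the cause decides what is written down, knowledge of the arm enters the count.

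Two further gaps add to this. Exacerbations are the main disease harm in this population, and those that occur during the 12 treatment weeks appear in neither the safety data nor the efficacy outcome. The follow-up year has no scheduled safety assessment, although the objective mentions the long term. Section 1 lists short follow-up and sparse safety reporting among the weaknesses of earlier trials, so this trial has its own reason to close these gaps.

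**Working it through.** The plan gives no safety figure to reproduce. The check sets the sections side by side, with one piece of schedule arithmetic.

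**1. Which events have a stated route into the data?**

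| Event | Section 2.7 event rule | Other stated route |
|---|---|---|
| Needling harm, weeks 0–12 | Covered | Table 1 safety row, weeks 4, 8, 12 |
| Change in vital signs or routine blood tests over treatment | Measured before and after; needs no attribution | – |
| Other event judged unrelated, weeks 0–12 | Not covered | None stated, except indirectly if medication changes (Section 2.5.1.3) |
| Exacerbation, weeks 0–12 | Excluded by the note | Medication change, or time and reason of discontinuation (Section 2.5.1.3) |
| Moderate or severe exacerbation, weeks 12–64 | Excluded by the note | Secondary outcome (Section 2.6.2.1, item 4) |
| Other event, weeks 12–64 | Covered only if associated with the intervention | No scheduled assessment; Section 2.7 follows up participants who abort |

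Three rows lack a systematic route: unrelated events during treatment, exacerbations during treatment, and events other than exacerbations in follow-up.

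**2. Schedule.** Inputs: 12 weeks of treatment and 52 weeks of follow-up (Section 2.2).

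- Total after baseline: 12 + 52 = 64 weeks, which matches the last visit in Table 1.
- Share of that time after the last scheduled safety assessment: 52 / 64 = 81%.
- Share covered: 12 / 64 = 19%.
- Visits after baseline with a safety mark: 3 of 5 (weeks 4, 8 and 12, but not 38 and 64).

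**3. Exacerbations during treatment.** The note in Section 2.7 removes them from adverse events. The outcome in Section 2.6.2.1 is confined to follow-up. Section 2.5.1.3 leaves a trace, as a medication change or a reason for discontinuation, but no section turns that trace into a count by arm.

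**4. Who judges association?** No section says. Section 2.8 gives the acupuncturist immediate management only. Section 2.4.3 states: "Patients, outcome assessors, data entry clerks and statistical analysts will be blinded". The therapist is not on that list, but neither is the therapist given the causality judgement.

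**5. A small mismatch.** Section 2.7 calls for vital signs and routine blood tests before treatment, while the safety row of Table 1 has no mark at week 0. The separate blood row is marked at weeks 0 and 12 and may cover the blood tests. Vital signs have no row of their own.

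**The case against.** The strongest reply is that the gap is smaller than it looks, for six reasons.

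- **Nothing is forbidden.** Section 2.7 says what must be reported promptly and does not bar other entries. Its later sentence on what follows an adverse event carries no limit by cause, and a note on exacerbations would hardly be needed if only needling injuries counted. This suggests a wider intention, but the only recording rule given is still worded by association. A centre that follows it exactly would omit unrelated events.
- **Recording may be blinded.** Section 3 says that outcomes are registered and measured by staff unaware of the groups. A reader might infer that the unblinded acupuncturist decides what is recorded, and the article does not support that inference. Equally, the sentence concerns outcomes and does not settle who records adverse events.
- **Much can still be compared.** A reader might infer that the safety objective cannot be answered at all. That goes too far, because needling harms, vital signs and blood tests to week 12, and exacerbations in follow-up, are collected in both arms.
- **Puncture events differ truly.** Less bleeding with a needle that stays outside the skin is an effect of treatment and not an ascertainment bias. This stands.
- **The objective is ambiguous.** Long-term may qualify efficacy alone, and Section 3 describes the follow-up year in terms of clinical indicators and exacerbations. This stands as a possible reading, which is why narrowing the objective is an acceptable remedy.
- **This is a condensed article.** Event forms and causality grading may sit in the full protocol, so their absence is no finding. The point here concerns the scope and the schedule that the article does state.

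**Conclusion.** The point holds in a limited form. The stated rule collects adverse events by association with the intervention, leaves out exacerbations, and is paired with a schedule that stops at week 12. Followed literally, three things are lost to the safety comparison: events judged unrelated, a count by arm of exacerbations during the 12 treatment weeks, and systematic collection over the 52 follow-up weeks (81% of the 64 weeks after baseline).

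This rests on two assumptions: that sites apply the recording sentence as written, and that the Table 1 marks read as weeks 4, 8 and 12. The conflict with Section 2.1 also requires long-term to apply to safety as well as efficacy.

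Arm-dependent bias is possible but not shown. The article gives no event rates and no attribution procedure, so its size and direction cannot be calculated. The primary outcome is unaffected. The matter deserves correction because it bears on a stated objective and cannot be mended at analysis.

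**What to change.** 1. In Section 2.7, require that every untoward event be recorded in both arms, whatever its presumed cause, from the first session to week 64.
2. Keep exacerbations distinct if preferred, but tabulate those in the treatment period by arm as a separate line.
3. Have relatedness classified afterwards by blinded personnel already in the trial, such as the outcome assessors. Present all-cause and related events by arm. The all-cause table matters because a description of bleeding or haematoma may itself hint at the arm.
4. Add the safety item to Table 1 at weeks 38 and 64, or reword Section 2.1 so that the safety objective covers the treatment period only.
5. Reconcile the baseline safety measurements in Section 2.7 with the week 0 column of Table 1.

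The cost is additional case report form entries, one item at two visits that already take place, and a short causality review. No new visits are needed. If the objective is narrowed instead of adding the two assessments, the trial gives up any claim to systematic safety data after treatment.

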##### 2.5.1.1 Manual acupuncture (MA) group

Patients in the MA group will choose a prone treatment position. After skin disinfection, the acupuncturist will insert the needle into the acupoint through the rubber base adhered to the acupoint. The direction and angle of acupuncture will be strictly under the basic requirements of acupuncture operation. 0.5-cun acupuncture needles (0.25 × 13 mm, Hwato, Suzhou, China) will be used to insert in a depth of 10–15 mm for the BL13. 1-cun acupuncture needles (0.25 mm × 25 mm, Hwato, Suzhou, China) will be used to insert in a depth of 15–20 mm for the EX-B1, LU1, and BL20. 1.5-cun acupuncture needles (0.25 mm × 40 mm, Hwato, Suzhou, China) will be used to insert in a depth of 25–30 mm for the BL23, ST36, and ST40. After needle insertion, a modest twisting and lifting maneuver will be performed to obtain a sensation of *deqi* (soreness, numbness, distension or heaviness) (44). The degree of *deqi* sensation will be assessed immediately after the patient having *deqi* sensation (45). The needles will be retained for 30 min each time, and *deqi* sensation operation will be performed every 10 min for 15 s each time. Treatments will be given 3 times per week (1–2 days apart) for a total of 12 weeks.

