##### 2.5.1.3 Basic treatment and medication changes

During the baseline period, all details of medications used by the patients to treat COPD and other underlying conditions will be recorded on a case report form (CRF), including the name of the medication, the dosage used, the frequency of use, the route of administration, and when the medications begin and end. Any changes in the patient’s medications throughout the study period will also be recorded in detail. If the patient experiences an acute exacerbation, the possibility of continuing acupuncture treatment will be assessed by a respiratory medicine specialist. If an acute exacerbation occurs that necessitates the application of antibiotics or hospitalization to control the infection, the trial will be discontinued and the time and reason for being discontinued will be recorded by the investigators.

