### 2.8. Management of acupuncture-related adverse events

The acupuncturist will take immediate action for adverse events related to acupuncture. In the event of minor adverse events such as localized bleeding and mild pain, the acupuncturist will apply pressure to the bleeding area to stop the bleeding and observe and reassure the painful area. In the event of a serious adverse event such as needle breakage or fainting, the patient will be quickly transported to the emergency room. Depending on the circumstances, the emergency room medical staff will take appropriate measures such as surgery, anti-infection treatment and emergency resuscitation to deal with the situation. Close monitoring of the patient’s condition and follow-up examinations will be conducted to ensure recovery.

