## 3 Discussion

COPD is a major public health problem. It not only seriously affects the health and life quality of patients, but also imposes a heavy burden on families and society. There are concerns about side effects and patient compliance with the long-term use of conventional drug regimens. Therefore, the combined use of complementary alternative therapies is expected to help alleviate these problems. However, the available evidence suffers from study design flaws and the mechanisms by which acupuncture works have not been well understood. The aim of this trial is to reassess the efficacy of acupuncture as an adjuvant therapy for COPD and explore the mechanisms of acupuncture efficacy from a perspective by gut microbiota, metabolome and inflammation.

In this study, patients with stable COPD are selected as the research population. COPD has a long disease duration, with high rates of disability and death (54). And the frequent recurrence of acute exacerbations of COPD is an important factor which affects the prognosis of condition and leads to death (55). Therefore, interventions during the stabilization period to prevent and reduce acute exacerbations can result in the most meaningful management of the condition for patients.

A set of commonly used, safe and effective acupoints in the clinic are selected for this trial (56, 57). LU1 and BL13 are the back-shu point and front-mu point of the lungs, respectively, which are key points for regulating the essence and function of the lungs, as well as projections of the anatomical location of the lungs on the body surface (58). EX-B1 is a particular acupoint for the treatment of asthma and dyspnea selected based on the long-term experience of clinicians. BL20 and BL23 tonify the spleen and kidney, respectively. ST36 is the most used acupoint for treating COPD besides BL13 (57). Together with BL20 and BL23, it increases the synergistic effect of regulating the lungs, spleen and kidney. Additionally, ST36 can nourish the healthy *qi* then enhance the immunity of COPD patients during the stable period. Studies have shown that ST36 can regulate the gut microbiota and reduce inflammation in the body (59, 60). ST40 works to resolve phlegm and achieve symptomatic treatment.

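### During the 12 needling weeks an event labelled an exacerbation is counted neither as an adverse event nor as an outcome, and no record asks whether needling caused it

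*Protocol article*

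**What the plan says.** **Adverse events.** Section 2.7 covers "Adverse events (AEs) associated with the intervention", gives examples "including bleeding, hematoma, needle breakage, local infection, persistent pain, syncope, etc., must be reported promptly and recorded in the CRFs", and requires serious cases to reach the project office and the ethics committee within 24 hours. It then adds: "Note: acute exacerbation of COPD is not counted as an adverse event". The note has no time limit and no condition on cause. Section 2.8 gives its serious examples in the same open form: "In the event of a serious adverse event such as needle breakage or fainting".

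**Exacerbations as an outcome.** Section 2.6.2.1, item 4, counts moderate or severe exacerbations in the follow-up period. Table 1 schedules that count at weeks 38 and 64 only. The scheduled safety assessments are at weeks 4, 8 and 12.

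**Exacerbations during treatment.** Under section 2.5.1.3, if one occurs, "the possibility of continuing acupuncture treatment will be assessed by a respiratory medicine specialist". Medication changes are recorded throughout. Discontinuation because of antibiotics or hospital admission is recorded with its time and reason.

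**Needling.** Section 2.5.1.1 gives the depths at two of the points: for one, the needle "will be used to insert in a depth of 10–15 mm for the BL13", and for the other it "will be used to insert in a depth of 15–20 mm for the EX-B1, LU1, and BL20". The Discussion describes LU1 and BL13 "as well as projections of the anatomical location of the lungs on the body surface". The sham needle does not pierce the skin (section 2.5.1.2 and Table 3).

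**The concern.** Leaving a disease event out of the adverse-event count is reasonable when it is already counted as an outcome, because nothing is lost. Here the two rules do not cover the same period. The exemption runs through the whole study, while the outcome count starts only after needling has ended.

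During treatment, the label alone decides whether an acute respiratory event is counted at all. No step asks whether needling played a part before the label takes effect. Only one arm receives needles that pierce the skin, some of them over what the protocol calls the surface projection of the lungs. An undercount of needling-related events would therefore favour that arm.

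Safety is part of the first objective (section 2.1), and the Introduction criticises earlier trials for reporting little on it. A safety comparison that omits treatment-phase exacerbations in both arms answers that objective only in part.

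**Working it through.** The plan states no figure on this point, so there is none to reproduce. The check sets the rules side by side and then describes the exposure.

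**Step 1. Which count covers which period**

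| Record | Weeks 0 to 12 | Follow-up, to week 64 |
|---|---|---|
| Needling sessions | 12 weeks × 3 = 36 | 0 |
| Scheduled safety assessment (Table 1) | weeks 4, 8, 12 | none |
| Exacerbation as adverse event (2.7) | exempt | exempt |
| Exacerbation as outcome (2.6.2.1, Table 1) | not counted | weeks 38, 64 |
| Other trace (2.5.1.3) | medication changes; specialist's view on continuing; time and reason if discontinued | medication changes |

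In follow-up the exemption is matched by a count. In weeks 0 to 12 it is not. That is 12 of 64 weeks, but 36 of 36 sessions.

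**Step 2. What the remaining trace contains**

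Discontinuation under 2.5.1.3 is tied to antibiotics or hospital admission. Under the definitions in 2.6.2.1, a moderate exacerbation may be treated with oral corticosteroids without antibiotics, and a severe one may be an emergency-room visit without admission. Neither meets the discontinuation trigger as worded. Such events leave a medication entry and perhaps the specialist's view on continuing. Where a discontinuation is recorded, its reason would be the exacerbation itself. No item asks about cause.

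**Step 3. Exposure at the two points over the lungs**

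- LU1 and BL13, both sides: 2 × 2 = 4 insertions per session.
- Per patient: 4 × 36 sessions = 144.
- Manual acupuncture arm: 144 × 36 patients = 5,184, if every patient attends every session.
- Sham arm: 0 insertions through the skin.

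This is planned maximum exposure. It is not a risk.

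**Step 4. How many exacerbations could fall in the gap**

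The documents give no exacerbation rate. For illustration, assume one moderate or severe exacerbation per patient-year. This borrows from the Table 2 criterion of at least one in the past year, a criterion missing from the list in section 2.3.2.1. Then 36 × 1 × 12/52 = 8.3 per arm. At 0.5 per year the figure is 4.2, and at 1.5 per year it is 12.5. The stability and antibiotic-free entry criteria may lower it. These are exacerbations of any cause. The documents give no basis for saying how many, if any, would be related to needling.

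**Step 5. What an arm of 36 can show**

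One case is 1/36 = 2.8%. With zero cases the exact one-sided 95% upper bound is 1 − 0.05^(1/36) = 8.0%. Both figures hold for any harm in any arm of 36, so they describe the arm size and do not measure this gap.

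**The case against.** The strongest reply is that the note exempts exacerbations, not injuries. A lung puncture is not an exacerbation. It is an event associated with the intervention, and the lists in 2.7 and 2.8 are open-ended. Once recognised it must be reported, and within 24 hours if serious. A reader might infer that lung puncture is unreportable because it is not named, but the text does not support that. This is also a journal article, and a fuller event list may well sit in the full protocol or the CRF, so the missing name is not a finding.

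Second, no section says that a needling injury would be taken for an exacerbation. That route is clinically plausible, but it comes from outside the documents. The Discussion's remark about LU1 and BL13 explains why the points were chosen and says nothing about risk.

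Third, events do leave traces: the specialist's assessment, medication changes, reasons for discontinuation, continued follow-up of those who stop, and monitors who check CRFs. The exemption is from adverse-event and 24-hour reporting, not from all recording.

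All three replies stand, and they limit the point. They do not remove it. The mismatch in Step 1 follows from rules the article states, and none of the traces is a count by arm or a judgement of cause.

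Separately, section 2.5.1.1 pairs a depth of up to 15 mm at BL13 with a 13 mm needle. Those figures must be reconciled, but this point does not depend on them.

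**Conclusion.** The point holds as a recording gap limited to the treatment phase. From the first session to week 12, an event labelled an exacerbation is in neither the adverse-event count nor the efficacy count, and its cause is not asked. If a needling-related respiratory event were given that label, it would also miss the 24-hour report. That could bias the safety comparison in one direction only, because skin-piercing needles are confined to one arm.

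The structural part is certain on the text: every session falls in the uncovered period. The effect on the safety result is not quantified. It depends on how often such an event occurs and how often it is mislabelled, and the documents give neither. A reader might go further and infer that a clean thoracic safety result would be produced by the coding rule. The documents do not support that, since a recognised injury is already reportable. This is an inexpensive improvement to a stated rule. It does not show that harm will be hidden.

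**What to change.** Change recording only:

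1. Limit the exemption in section 2.7 to the follow-up period, where exacerbations are a counted outcome.
2. From the first session to week 12, enter every exacerbation or acute respiratory worsening on the adverse-event page, in both arms, with the time since the last session.
3. Have the respiratory specialist already involved under section 2.5.1.3 record a judgement of relatedness to needling. Make the entry whatever that judgement is. Section 2.7 otherwise covers only intervention-associated events, and those judged unrelated would drop out again.
4. Tabulate these events by arm.

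Naming pneumothorax in sections 2.7 and 2.8 is an optional clarification.

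The cost is one CRF field and a slightly higher adverse-event count, most of it probably ordinary exacerbations in both arms. Investigation, treatment and decisions on continuing acupuncture stay with the investigators.
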